### Recruitment {15}

Participants with stable conditions are selected, and the participants are accurately defined.Disease status and related variables are accurately measured.Investigators and clinical trial coordinators should receive training to ensure that participants are selected and excluded strictly according to protocol, and studies are conducted according to protocol.Recruited from a population at high risk for post-operative RVF.To improve the identification of participants based on the historical data and literature reports of the study group.

## Assignment of interventions: allocation

### Sequence generation {16a}

Randomization occurs after recruitment. Participants are randomized to Group A (experimental group) and Group B (control group) using a computerized random number generator in R software by a research assistant, which divides eligible participants into Group A or Group B with a 1:1 ratio.

### Concealment mechanism {16b}

Allocation will be concealed, and envelopes with participant numbers containing the group allocation are prepared and opened by different research assistants in front of the participants after formal consent is obtained. Both the research assistant and the participant do not have prior knowledge of the group allocation details.

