## Interventions

### Explanation for the choice of comparators {6b}

This trial will compare the efficacy of preventing RVF. Compared to the control group, the experimental group would add a step to an operation of packing with a dislocated fat flap containing ovarian vascular pedicle anterior. The operations will be performed by the same clinic doctor of the trial at Fujian Medical University Union Hospital. It has the advantages of not being easily perceived by the patient and a higher feasibility of operation.

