### Implementation {16c}

An independent researcher, blinded to the study protocol, will generate the allocation sequence. Another researcher will give the opaque envelope to the surgeon according to the timing sequence of participant registration for the trial. Then, the surgeon will open the envelope to perform the corresponding operation.

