## Assignment of interventions: blinding

### Who will be blinded {17a}

Patients are not blinded. Caregivers are not blinded. Statisticians will not know the allocation.

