### Plans to promote participant retention and complete follow-up {18b}

The research assistant will contact participants via telephone call (or other contact means such as emails or text messages) to complete the later stages of the follow-up questionnaires. The research assistant also will monitor the retention rate and reasons for discontinuation of the study (e.g., consent withdrawn, lost to follow-up).

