### Data management {19}

Researchers must ensure that the privacy of participants. In all documents, only the identity of the clinical study subject should be identified, and the name and hospitalization number of the subject should not be indicated. The investigator must maintain the names, addresses, and records of all participants involved in the clinical trial. The raw data will be collected by assessors who are blinded to the group assignment and repeated input methods will be used to ensure that the entered data is correct. These data will be kept strictly by the researchers.

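### Two incompatible procedures for opening the allocation envelope: one discloses the arm before surgery and leaves the promised blinded data collection unprotected

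*Protocol article*

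**What the plan says.** All references are to the protocol article.

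- **Sequence generation {16a}:** a research assistant randomises participants with a random number generator in R.
- **Concealment mechanism {16b}:** the envelopes are "prepared and opened by different research assistants in front of the participants after formal consent is obtained". It adds that neither the assistant nor the participant knows the allocation beforehand.
- **Implementation {16c}:** the sequence comes from an independent researcher who does not know the protocol. A further member of the team passes the envelope, which is opaque, to the surgeon in order of registration. The section goes on: "Then, the surgeon will open the envelope to perform the corresponding operation".
- **Who will be blinded {17a}:** "Patients are not blinded. Caregivers are not blinded. Statisticians will not know the allocation". Outcome assessors are not mentioned.
- **Data management {19}:** "The raw data will be collected by assessors who are blinded to the group assignment".
- **Plans to promote participant retention {18b}:** "The research assistant will contact participants via telephone call", or by email or text message, to complete the later questionnaires.
- **Explanation for the choice of comparators {6b}**, on the added flap step: "It has the advantages of not being easily perceived by the patient and a higher feasibility of operation".
- **Handling of withdrawals:** Concomitant care {11d} and Statistical methods {20a} leave drop-outs out of the analysis, and {20c} restricts it to complete cases.

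**The concern.** Site staff need one procedure for the envelope, and the article gives two. They differ on who opens it, when, and whether the participant sees the result.

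Two things are at stake if {16b} is the one followed.

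1. **Withdrawal.** A participant who learns her arm between consent and surgery can leave because of it. Since the analysis drops withdrawals, such departures would remove participants from one arm for a reason linked to allocation, and the groups compared would no longer be the groups randomised.
2. **Outcome collection.** Quality of life and abnormal vaginal discharge are secondary outcomes open to subjective reporting. The Background {6a} describes rectovaginal fistula (RVF) by symptoms that a patient would notice. Blinded data collection is the plan's safeguard here, but nothing keeps the people who see allocations away from the people who collect outcomes.

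**Working it through.** The point rests on the wording, so the check sets the sections side by side.

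**1. Can {16b} and {16c} both be followed?**

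| | {16b} | {16c} |
|---|---|---|
| Who opens | Research assistants | Surgeon |
| When | After consent | To carry out the operation |
| Participant present | Yes | Not stated; no such role given |

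An envelope already opened in front of the participant cannot reach the surgeon unopened. No second envelope or resealing step is described. The two accounts are incompatible.

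**2. Who makes the sequence?** {16a} names a research assistant and {16c} an independent researcher. One person could fit both labels, so this is an ambiguity to clear up and weaker than item 1.

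**3. Does {16b} disclose the arm before surgery?** Yes, to the participant and to the assistant who opens the envelope. {6b} describes the added step as hard for the patient to notice, so the operation itself does not force this disclosure.

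**4. What happens to a participant who then withdraws?** A request to withdraw is a listed reason for discontinuation in {11b}. Under {11d}, {20a} and {20c} she is not analysed.

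**5. Is blinded collection under {19} protected?** Research assistants take part in consent ({10}, {26a}), open envelopes ({16b}) and make follow-up contact ({18b}). The word different in {16b} shows that more than one assistant is involved. No section says that those who open envelopes are kept out of follow-up, and {17a} lists only statisticians as blinded. The claim in {19} therefore has no procedure behind it.

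**6. Scale.** The inputs are from Sample size {14}: 115 per group and 9.9% incidence.
- Expected control events: 0.099 × 115 = 11.4, about 11.
- One participant classified differently in one group: 1/115 = 0.87 percentage points.
- Three such participants, an arbitrary number for illustration: 3/115 = 2.6 percentage points.

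These figures show how much a few participants weigh. They do not estimate bias; the documents give no basis for that.

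**The case against.** The best defence is that patient unblinding is declared. {17a} says plainly "Patients are not blinded", and an open surgical trial with blinded assessors and a blinded statistician is a recognised design. This stands. The remark in {6b} sits awkwardly beside {17a}, but it shows at most that patients might have been kept unaware. Adopting {16c} alone would not blind them.

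It can also be said that a shared job title does not prove shared people. Several assistants are involved, {18b} concerns retention and later questionnaires and does not assign RVF assessment, and the assessors in {19} may be separate staff. This also stands. A reader might infer that blinded assessment is defeated, but no section says that an envelope opener assesses outcomes. The documents show only that the safeguard is unprotected.

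A reader might likewise infer that the primary endpoint is partly patient-reported. The symptoms in {6a} and the separate patient-reported forms in {18a} make this plausible, but no section says how RVF is ascertained.

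Nor do the documents show that allocation concealment at entry fails. Under {16b} the envelope is opened only after consent, and the section denies prior knowledge of the allocation.

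None of this answers the conflict between {16b} and {16c}, or the combination of disclosure before surgery with analysis rules that drop withdrawals.

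**Conclusion.** The contradiction between {16b} and {16c} is established from the text and should be resolved. The difference over the sequence generator needs clarifying at the same time. If {16b} is what happens, disclosure before surgery opens a route to allocation-driven withdrawal that the analysis would not capture. This conclusion takes {11d}, {20a} and {20c} to be applied as written; no such withdrawal is documented. The blinding claimed in {19} is unprotected, which is less than saying that it fails.

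The size of any effect is unknown. The 0.87 points per participant is scale only.

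Two wider conclusions may tempt a reader. The first is that leaving patients unblinded is an error. It is a stated design choice, for the sponsor to reconcile with {6b}. The second is that the envelope should be opened only once exploration has confirmed a usable flap. That is a different randomisation design, which {16c} does not contain, and correcting the contradiction does not require it.

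**What to change.** 1. Keep one procedure, that of {16c}: the independent researcher makes the sequence, and the surgeon opens the opaque envelope at operation. Bring {16a} into line, and delete from {16b} the opening by research assistants in front of participants.
2. State in {17a} that outcome assessors are blinded, so that it agrees with {19}.
3. State that anyone who generates, handles or sees allocations takes no part in collecting RVF, vaginal discharge or quality-of-life data. Apply this to the follow-up contacts in {18b}.
4. Reconcile {6b} with {17a} by saying whether patients are to be kept unaware of their arm. Either answer is open to the sponsor.

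**Cost.** The change is mainly one of wording, together with keeping allocation and follow-up duties apart. Under {25} it needs resubmission to the registry and renewed ethics approval, and participants must be informed and re-consented if the change departs from what they were told. Trial status reports 96 participants recruited, who may already know their arm, so the end to disclosure before surgery helps only later entrants. The separation of staff still helps for follow-up yet to come, since Table 1 runs to 60 months. Unless patients are also kept unaware, a participant who knows her arm can still reveal it to an assessor; the fix reduces that risk but does not remove it.

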### Implementation {16c}

An independent researcher, blinded to the study protocol, will generate the allocation sequence. Another researcher will give the opaque envelope to the surgeon according to the timing sequence of participant registration for the trial. Then, the surgeon will open the envelope to perform the corresponding operation.

## Assignment of interventions: blinding

### Who will be blinded {17a}

Patients are not blinded. Caregivers are not blinded. Statisticians will not know the allocation.

### Procedure for unblinding if needed {17b}

Not applicable. Because the researcher who is responsible for participant intervention will not turn a blind eye to the group assignment. Statisticians can be notified to delete data related to participants with a specific participant number.

## Data collection and management

### Plans for assessment and collection of outcomes {18a}

Case report forms (CRFs) will record all required information with separate CRFs collecting clinical and patient-reported information. Copies of CRFs used in the trial are available on request.

### Plans to promote participant retention and complete follow-up {18b}

The research assistant will contact participants via telephone call (or other contact means such as emails or text messages) to complete the later stages of the follow-up questionnaires. The research assistant also will monitor the retention rate and reasons for discontinuation of the study (e.g., consent withdrawn, lost to follow-up).

### Data management {19}

Researchers must ensure that the privacy of participants. In all documents, only the identity of the clinical study subject should be identified, and the name and hospitalization number of the subject should not be indicated. The investigator must maintain the names, addresses, and records of all participants involved in the clinical trial. The raw data will be collected by assessors who are blinded to the group assignment and repeated input methods will be used to ensure that the entered data is correct. These data will be kept strictly by the researchers.

### Confidentiality {27}

This study intends to sign a clinical trial informed consent prior to surgery to inform patients of their relevant rights and interests. Patients’ data included in this study will be confidential, patient specimens will be identified by study numbers rather than patient names, and patient information will not be disclosed to members outside the study team. No patient information will be disclosed when the study results are published. All patients in the experimental group have ovarian failure, and the study would not increase the additional risk and cost of patients, while the control group only has radical rectal cancer surgery, which would not increase the additional risk and cost of patients. We will protect the privacy of participants’ personal medical information as required by law. The staff in this study is also bound by this agreement.

### Plans for collection, laboratory evaluation, and storage of biological specimens for genetic or molecular analysis in this trial/future use {33}

Not applicable. This trial does not have biological specimens.

## Statistical methods

### Statistical methods for primary and secondary outcomes {20a}

The independent statistician is responsible for the statistical analysis with SPSS 24.0 software. Patient data that falls off will not be included in the analysis. In the statistical analysis, measurement data between the two groups will be analyzed with the *t*-test and rank-sum test, while categorical data will be analyzed with *χ*^2^ test. Data will be recorded as mean ± standard deviation or median (first quartile, third quartile). The experiment is a non-inferiority trial, and the statistical method is mainly based on “parameter estimation.” Using the primary endpoint, determine the confidence interval for the difference in the efficacy of surgical methods in preventing rectovaginal fistula between the control group and the cases group. The significance level used for statistical analysis will be two-sided with confidence intervals at the 95% level.

### Interim analyses {21b}

#### Objective

To comprehensively weigh the cost-risk relationship of this surgical method in preventing rectovaginal fistula from the perspective of the effectiveness and safety of the plan in the interim. To confirm whether the intervention can reach the study endpoint.

#### Samples

It is expected that the total number of samples would reach 80–100. The cases and controls were grouped according to the experimental protocol, and mid-term experimental data would be collected to analyze the expected risks of intervention measures. When adverse events or other related complications occur, patients who consider adverse outcomes would be reported by the research team and analyzed to determine whether their adverse events are related to the trial, and the research team would fulfill their obligation to inform and respect the patient's right to know related content. In the case of mid-term analysis, if there is no statistically significant difference between the case group and the control group or there are more adverse complications in the case group compared to the control group, the trial can be considered for discontinuation and protocol modification can be carried out. If there are significant modifications during the implementation process, the main researcher shall write and sign a “protocol modification manual” and submit it to the ethics committee for approval before implementation.

In the study, if the analysis results have no clinical significance due to the number of cases, the experimental time will be extended. The interim analysis report will be publicly released by the research participants.

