### Sample size {14}

Female patients with low and medium rectal cancer in the Department of Colorectal Surgery, Fujian Medical University Union Hospital, from April 2020 to March 2023 are selected as the research participants. It is assumed that the RVF of the study group is the same as that of the control group. According to previous research results and relevant literature reports, the incidence of RVF of the control group and the test group was set at 9.9%, the non-inferior margin value was set at 15%, the test level was set at 0.05, and the power was set at 0.8 [1, 2]. The sample size was calculated by SPSS24.0 software as follows: *N* = 115, and each group needed 115 people. We assume that 20% of patients would be lost to follow-up, and 144 would need to be enrolled.

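### The interim ground for discontinuation, no significant difference at 80–100 patients, is the result the equal-rates non-inferiority design expects, and it pulls against a results-driven extension with no stated limit

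*Protocol article*

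**What the plan says.** Interim analyses {21b}, under Samples, sets the timing: "It is expected that the total number of samples would reach 80–100". It then says that "the trial can be considered for discontinuation and protocol modification can be carried out" on either of two grounds: "if there is no statistically significant difference between the case group and the control group or there are more adverse complications in the case group". No significance level, boundary or size of excess is attached to either ground.

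The same section adds that "if the analysis results have no clinical significance due to the number of cases, the experimental time will be extended", and on publication: "The interim analysis report will be publicly released by the research participants".

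The design is set elsewhere. Sample size {14} states: "It is assumed that the RVF of the study group is the same as that of the control group". It adds that "the incidence of RVF of the control group and the test group was set at 9.9" (per cent), and that "the non-inferior margin value was set at 15%, the test level was set at 0.05, and the power was set at 0.8". Statistical methods {20a} calls the trial a non-inferiority trial resting mainly on estimation, with two-sided 95% confidence intervals. Objectives {7}, by contrast, asks whether the RVF rates differ significantly.

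**The concern.** A design that assumes equal rates and tests non-inferiority predicts a non-significant difference. Listing that outcome as a reason to stop or rewrite the trial turns the expected, favourable result into a warning. Under the difference objective in Objectives {7} the rule does no better, because the interim has too few events for non-significance to say anything about futility.

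The complications ground, as worded, compares counts with no margin for chance. The extension sentence gives the opposite response to an inconclusive result: carry on rather than stop. With no rule for choosing between the two, the choice would be made after the comparison has been seen. What is at stake is a trial that could be stopped or altered while on course, or prolonged because of its own result.

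**Working it through.** **Inputs.** From the documents: 80–100 patients at 1:1, so 40–50 per arm; RVF 9.9% in both arms; margin 15%, read as percentage points; χ² test for categorical data; two-sided 5% level and 95% intervals; 115 per group. Assumed: the interim difference is in RVF, all 40–50 per arm are evaluable, and the chi-square test is uncorrected.

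**The plan's own figure.** No operating characteristics are given for the interim. The one design figure is 115 per group. The usual non-inferiority formula gives n = 2p(1−p)(z₀.₉₇₅ + z₀.₈)²/m² = 2 × 0.099 × 0.901 × (1.960 + 0.842)²/0.15² = 62.2, so 63 per group (50 at one-sided 0.05). So 115 is not reproduced; that is a separate matter. The dropout step is reproduced: 115/0.8 = 143.75, or 144. Here 115 serves only as the starting size for step 5.

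**1. Events at the interim.** 40 × 0.099 = 3.96 and 50 × 0.099 = 4.95, so about 4–5 expected RVFs per arm. If the flap arm has none, the control arm needs at least 4 for chi-square significance (at 45 per arm, 4 v 0 gives 4.19 against the critical value 3.84).

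**2. Chance of meeting the non-significance ground.** Exact sum of binomial probabilities over all tables with chi-square p ≥ 0.05, control rate 9.9%:

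| Flap rate | 40 per arm | 48 per arm | 50 per arm |
|---|---|---|---|
| 9.9% (design) | 0.941 | 0.941 | 0.950 |
| 5% (assumed) | 0.858 | 0.833 | 0.859 |
| 3% (assumed) | 0.749 | 0.691 | 0.730 |
| 1% (assumed) | 0.563 | 0.452 | 0.474 |

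With Fisher's exact test the design row becomes about 0.98.

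**3. Overlap with success.** Non-inferiority is met when (pE − pC) + 1.96 × √[pC(1−pC)/n + pE(1−pE)/n] < 0.15. Example: 4/45 v 4/45 has difference 0 and SE 0.060, so the upper limit is 11.8 points. The margin is met, chi-square is 0, and the discontinuation ground is met as well. With equal 9.9% rates, 95.5% (40 per arm) to 96.5% (50 per arm) of the interim data sets that already meet the margin are also non-significant.

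**4. Complications ground.** With equal true rates, P(more in the flap arm) = [1 − P(tie)]/2. At 48 per arm this is 43.2%, 44.9% and 45.6% for assumed rates of 10%, 20% and 30%.

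**5. Extension, only if it led to unadjusted retests.** Assumed looks at 115, 173 (+58) and 231 (+116) per arm, 400,000 simulated trials:

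- Difference test at 9.9% v 9.9%: cumulative type I error 5.2%, 8.0%, 10.0%.
- Non-inferiority interval at 9.9% v 24.9%: 2.8%, 4.2%, 5.3%.

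**The case against.** The strongest reply is that the rule is permissive. Discontinuation can be considered; it is not required. Changes need a signed modification document and ethics approval, and termination rests with the monitoring expert or the principal investigator. This stands. The chance of meeting a ground is not the chance of stopping, and a reader who infers that the trial would probably end whatever the truth goes beyond the text. The figures above also fall to 45–56% at an assumed 1% flap rate. But a ground met in about 94% of trials under the design assumption gives the decision-makers no guidance.

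A charitable reader might take the ground to mean that non-inferiority has not been shown. The words refer to a difference between the groups. Even so read, the ground would be met in about 28–34% of equal-rate trials (the margin is met in 66–72% at 40–50 per arm).

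A reader might also infer that a non-significant final result leads to repeated, unadjusted testing. The documents do not support that. The extension sentence speaks of clinical significance, stands under the interim analysis and mentions no retest. Prolonging recruitment to reach the planned number is a natural reading, in line with the provision under Trial status for insufficient recruits. Any alpha adjustment could sit in an analysis plan that is not shown.

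Two further limits stand. The section also has adverse events assessed for relation to the trial, so a numerical excess need not act alone. And it does not say that the public interim report is by arm, or that it appears during recruitment.

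**Conclusion.** The non-significance ground must be changed. It contradicts the equal-rates non-inferiority design, where it is met in 94–95% of trials, and it is a poor futility rule under the difference objective (83–86% when RVF is halved). The design-row figure rests on the protocol's own rates and on chi-square at 40–50 evaluable patients per arm; the 5% flap rate is assumed. No reading of the framework rescues the rule, and since the protocol fixes this criterion itself, it is not a detail left to an analysis plan.

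The other parts are weaker. The complications ground lacks a threshold, and its 43–46% depends on assumed complication rates. The extension depends on results, has no stated cap, and conflicts with the discontinuation ground. The rise in type I error to about 8% and 10% (difference test), or 4.2% and 5.3% (non-inferiority test), is conditional on assumed retests and is not a property of the plan as written. The public-release sentence needs a safeguard, since patients and caregivers are unblinded, but it does not establish that comparative results will be released early.

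**What to change.** - Delete non-significance as a ground for discontinuation. Put in its place a non-binding futility guide tied to the final primary non-inferiority test, such as conditional or predictive power, with the threshold set by the trial statistician and no efficacy claim at the interim. State the effect under which it is calculated: by the standard formula, power at 115 per arm with the stated inputs is about 97%, so conditional power under equal rates would seldom fall low.
- Have the statistical summary of complications give the estimated difference with its confidence interval, reviewed by the monitoring expert, rather than rest on a bare numerical excess.
- Reconcile the discontinue and extend sentences. Limit any extension to reaching the planned size, or to one pre-stated review of the pooled, arm-blind RVF rate, followed by a single final test.
- State that by-arm interim results are withheld from public release until the final analysis.

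The cost is rewording one section and one power calculation. The downside is that the sponsor gives up the freedom to stop or extend on the observed comparison. Timing matters: Trial status reports 96 recruited, already inside the 80–100 window, so the amendment should state whether the interim look has taken place and what was seen.

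### The protocol commits to public release of a comparative interim report with no embargo, at a point when recruitment and follow-up are still open

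*Protocol article*

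**What the plan says.** In the protocol article, Interim analyses {21b}, the Objective subsection gives the interim the task of weighing effectiveness and safety. The Samples subsection sets its timing ("It is expected that the total number of samples would reach 80–100") and bases the decision on two comparisons between the groups: statistical significance and the number of adverse complications. Discontinuation and modification may be considered. If the case numbers leave the results inconclusive, "the experimental time will be extended". The subsection ends: "The interim analysis report will be publicly released by the research participants". It does not say when. It is also unclear whether the last words mean the researchers or the patients.

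On knowledge of allocation, Who will be blinded {17a} says "Patients are not blinded. Caregivers are not blinded" and adds that statisticians will not know the allocation. Under Implementation {16c} the surgeon opens the envelope. Data management {19} says that assessors blinded to group collect the raw data.

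On timing, Sample size {14} says "each group needed 115 people" and then "We assume that 20% of patients would be lost to follow-up, and 144 would need to be enrolled". Trial status reports 96 patients recruited, with recruitment expected to finish at the end of 2023 and possibly to be extended. Table 1 schedules assessment of rectovaginal fistula (RVF) from 3 to 60 months.

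**The concern.** Comparative interim results are normally kept from the people whose behaviour can alter the rest of the trial. Here the protocol promises the opposite, and several of its own provisions give published results a way to act:

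- **Consent.** Patients approached after release would decide with arm results in view.
- **Withdrawal.** Patients know their group and may withdraw at any time. Sections {11d} and {20a} remove dropouts from the analysis, and {20c} restricts it to complete cases. Withdrawal that differs by arm would therefore change the primary comparison directly.
- **Delivery of the intervention.** Section {11b} lets the surgeon leave the allocated procedure on findings during the operation, for example when no suitable flap is available. A surgeon who has seen the interim result may apply that judgement differently.
- **Patient reports.** Vaginal discharge and quality of life are secondary outcomes, and under {18b} later questionnaires are completed by telephone or message. Patients who know both their group and the published result may answer differently.

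Once results are public, none of this can be undone in the analysis.

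**Working it through.** **Inputs.** 115 per group, 20% loss and a target of 144 (Sample size {14}); interim at 80–100 patients in total (Samples); 96 recruited (Trial status); 1:1 allocation (Trial design {8}); RVF incidence of 9.9% in both groups (Sample size {14}).

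**The plan's enrolment figure.** 115 / (1 − 0.20) = 143.75, rounded up to 144. This reproduces the stated 144 as a per-group figure, so total enrolment is 2 × 144 = 288. The sentence itself does not say per group, so the other readings are shown too. I take 115 as stated; whether it follows from its own inputs is a separate matter and does not affect this point.

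**Share still to enrol at the interim** = (total − interim n) / total:

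| Total | Interim at 80 | At the 96 recruited | Interim at 100 |
|---|---|---|---|
| 288 (144 per group) | 208 (72%) | 192 (67%) | 188 (65%) |
| 230 (115 per group, no loss) | 150 (65%) | 134 (58%) | 130 (57%) |
| 144 (read as the total) | 64 (44%) | 48 (33%) | 44 (31%) |

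The interim falls during recruitment in every row. Most of the sample is still to come in the first two rows but not in the third.

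**Follow-up still open.** Recruitment began in April 2020. By the end of 2023 the earliest patient would have at most about 45 months of follow-up, short of the 60-month visit. So no patient would have completed the schedule while recruitment was open.

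**Information in the released report.** With 1:1 allocation, 80–100 patients means 40–50 per arm. Expected RVF per arm: 40 × 0.099 = 3.96 and 50 × 0.099 = 4.95, so about 4–5. This assumes that every patient has been followed long enough to show the full 9.9%, a figure tied to no time point; with incomplete follow-up there would be fewer. As a rough guide, the 95% half-width for the difference between arms is 1.96 × √(2 × 0.099 × 0.901 / n):

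- n = 40: 1.96 × 0.0668 = 0.131
- n = 50: 1.96 × 0.0597 = 0.117

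That is about 12–13 percentage points either way, more than the assumed incidence itself. The normal approximation is crude with so few events, but the order of magnitude is clear.

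**The case against.** The strongest case on the other side is that the text is being made to say more than it does. Much of this stands.

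- **Release date.** A reader might infer that the protocol schedules publication during recruitment. It states no date. The inference is strong, because an interim report is tied to 80–100 patients and nothing delays its release, but it remains an inference. Nor does the text say that the report tabulates results by arm; that follows from the comparison it is meant to report. Continuation is likely but not assured.
- **Blinding.** A reader might call the whole trial unblinded. Data collectors and statisticians are stated to be blinded, and arm-level results do not by themselves tell a blinded assessor which group a patient is in. The exposed parties are patients, caregivers and the surgeon, although an assessor could learn a patient's group from one of them.
- **Primary outcome.** A reader might infer that RVF is diagnosed from symptoms and that its ascertainment is therefore biased. The introduction describes how RVF manifests, but the Outcomes section gives no diagnostic rule, so this cannot be asserted. The better-supported reporting concern is with discharge and quality of life.
- **Comparability before and after release.** A change in who consents acts on both concurrently randomised arms and mainly affects generalisability. The threat to the comparison between arms comes from behaviour after allocation is known.

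None of this supplies an embargo or an access limit, and no other section does so. If delayed release was intended, the text needs to say so.

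**Conclusion.** The concern holds in this limited form. The protocol commits to public release of a comparative interim report without embargo or access restriction, and by its own numbers the interim comes while patients are still being enrolled and followed. The share still to enrol is 65–72% if 144 is per group, which the arithmetic supports, and 31–44% if it is the total. It is therefore not established on every reading that most patients enrol after the interim.

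The exposure runs through consent, differential withdrawal, the surgeon's intraoperative decision and patients' own reports. The size and direction of any resulting bias cannot be calculated from the document. The conclusion assumes that release follows the interim reasonably promptly and that the report shows results by arm; the wording permits both but states neither. The imprecision of about 4–5 events per arm assumes complete follow-up at 9.9%. This should be changed, and before the interim report is issued.

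**What to change.** Replace the release sentence in Samples with a provision to this effect:

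- The statistician prepares the comparative interim results with coded arms, which keeps {17a} intact, and they go only to the monitoring expert.
- Investigators, participants and the public receive only the decision: continue, modify or stop.
- The interim report is released after recruitment and primary-outcome follow-up are complete. Table 1 assesses RVF at many visits, so the sentence should name the visit that counts as completion.
- Safety information that participants need reaches them through the ethics committee, which preserves the duty to inform already stated in Samples.

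Sections {5d} and {21a} need to be aligned with this. Both give the monitoring expert the final word on termination and also give the principal investigator any final decisions; they should state who decides on the interim results without passing those results on.

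The cost is later publication of the interim data and small conforming edits to these sections. The sample size and the final analysis do not change.
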